#### Neuroimaging

Before the first tDCS stimulation session, participants underwent resting-state functional MRI (fMRI) data acquisition, which was repeated immediately after the completion of the stimulation series, following the 90^th^ day.

fMRI will evaluate structural and functional connectivity, with a specific focus on the default mode network (DMN), parietal memory network (PMN), and hippocampal connectivity. Network entropy will be computed using both Shannon and permutation entropy approaches.

R4 In detail, the processing step of the structural and functional connectivity will follow using the FreeSurfer (2025) and CONN Toolbox (2025). EEG pre-processing and connectivity analyses will follow standardized pipelines using open-source software (e.g., EEGLAB). Given the previous literature indicating the role of underlying connectivity and electrophysiological features of non-impaired structural brain regions in early dementia, we will pay special attention to the connectivity analysis. This will be assessed both at the ROI-to-ROI level and through whole-brain network analyses using the CONN Toolbox, with a focus on the parietal memory network (PMN) and default mode network (DMN). Entropy measures will be derived from resting-state correlation matrices to capture network complexity and integration. The calculation for different types of entropies will be performed according to the previously defined codes by Rostaghi and Azami (2016), which have already been used in our previous study (Yulug et al., 2025). The correction for multiple comparisons, family-wise error correction, will be applied, while for ROI-based analyses, correction will be used across the predefined set of regions to minimize false positive values.

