## Evaluation of the hypothesis

As briefly mentioned above, the primary endpoint of this study is the effect of anodal tDCS on cognitive improvement in patients with MCI, as measured by changes in performance on a standardized neurocognitive test battery. Composite *z*-scores will be derived for parietal memory network–related memory measures (primary composite outcome) and executive-function tasks (key secondary cognitive outcomes). Cognitive assessments will be performed at baseline, immediately after the intervention (Day 14), and at follow-up (Day 90).

The secondary endpoints are the neural correlates of stimulation-induced cognitive changes, assessed through multimodal neuroimaging and electrophysiological measures. Resting-state functional MRI will be used to evaluate alterations in structural and functional connectivity within the default mode network (DMN), parietal memory network (PMN), and hippocampal regions, alongside entropy measures (Shannon and permutation entropy). Quantitative Electroencephalogram (EEG) will be used to capture changes in electrophysiological activity, including power spectral density, coherence, and network connectivity indices. These secondary measures will provide connection insights into the network-level effects of tDCS and their relationship to cognitive outcomes.

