### EEG (electroencephalogram)

*EEG Power Spectrum Analysis;* EEG data will be separated into one-second epochs after they are cleared of noise. Power spectrums of these data will be obtained in the delta, theta, alpha, beta and gamma frequency bands. Each epoch will be analyzed using the Fast Fourier Transform (FFT) with a 10% Hanning window. Subsequently, power spectrum analysis will be performed to obtain the frequency values for each electrode by averaging all FFTs. Maximum peaks will be determined in the delta (0.5–3.5 Hz), theta (4–7 Hz), alpha (8–13 Hz), beta (15–28 Hz), and gamma (28–48 Hz) frequency bands. These values will be used in statistical analysis for each person and electrode.

*EEG Coherence Analysis:* Coherence measurements at delta, theta, alpha, beta, and gamma frequencies can be analyzed for either intra-hemispheric electrode connections or inter-hemispheric electrode connections. Coherence values take values between 0 and 1. Values close to 0 indicate that there is no connection at the determined frequency between the two calculated electrode regions. In comparison, values close to 1 indicate a high coupling between the two electrode regions. Coherence calculation will be performed using the Brain Vision Analyzer program.^1^ The data obtained during memory and visualization tasks will be separated into one-second epochs after being cleared of noise. Power spectrums of these data will be obtained in the delta, theta, alpha, beta and gamma frequency bands. Fast Fourier Transform will analyze each epoch with a 10% Hanning window. Then, these data will be calculated for all possible electrode pairs using the Brain Vision analysis program with the formula given below.

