*EEG functional connectivity analysis:* eLORETA software will be used for functional connectivity analysis. sLORETA/eLORETA is an online, ree software developed by Roberto Pascual-Marqui and his team^2^ (Pascual-Marqui et al., 1994). eLORETA is an algorithm developed to solve the inverse problem and it does not contain localization bias even in the presence of noise. In this software, resting state data with eyes closed, separated into 2-s epochs, whose artifacts are cleaned by pre-processing, will be used. The relevant areas to be analyzed in the cortical plane and the relevant frequency band gaps will be determined. The time series containing the eLORETA current source density obtained from these areas will be calculated, and a “lagged linear coherence” matrix will be created to be applied in graph theory (Vecchio et al., 2016). “Lagged linear coherence” will give correct physiological connectivity, unaffected by volume conduction and low spatial resolution.

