### Statistical analyses

All statistical analyses will be conducted using IBM SPSS Statistics, version 29.0 (IBM Corp., Armonk, NY, United States).

Analyses will be performed stratified by diagnosis (AD-MCI and PD-MCI):

*Neurocognitive outcomes:* Within each diagnosis group, repeated-measures ANOVA/GLM will be used with Time (Baseline, Day 14, Day 90) as a within-subject factor, Group (Real vs. Sham) and Target (DLPFC vs. LPC) as between-subject factors, and age, sex, education, and baseline global cognition as covariates. Planned contrasts will test the Group × Target × Time interaction separately in AD-MCI and PD-MCI. Between-diagnosis comparisons will then examine whether the effect of stimulation differs between AD-MCI and PD-MCI by including Diagnosis (AD-MCI vs. PD-MCI) as an additional between-subject factor. Post-hoc tests will be adjusted with Bonferroni correction.

*fMRI outcomes:* Resting-state fMRI data will be analyzed separately within AD-MCI and PD-MCI groups to assess functional connectivity within DMN, PMN, and hippocampal regions, as well as entropy metrics (Shannon and permutation entropy). Longitudinal changes (Baseline, Day 14, Day 90) and group differences (Real vs. Sham; DLPFC vs. LPC) will be assessed using repeated-measures ANOVA/ANCOVA with the same covariates.

After stratified analyses, diagnosis will be included as a factor to test for Diagnosis × Group × Target × Time interactions.

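### Three secondary measures are described with a source or setting that does not support them as written, chiefly permutation entropy taken from a correlation matrix

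*Protocol article*

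**What the plan says.** **Entropy.** The Neuroimaging section states: "Network entropy will be computed using both Shannon and permutation entropy approaches". Later in the same section it gives the input for these measures without distinguishing the two types: "Entropy measures will be derived from resting-state correlation matrices to capture network complexity and integration". It adds that the calculations follow published code already used in an earlier study by the group. Statistical analyses then treats both as outcomes; the fMRI models are to "assess functional connectivity within DMN, PMN, and hippocampal regions, as well as entropy metrics (Shannon and permutation entropy").

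**Structural connectivity.** Evaluation of the hypothesis lists among the secondary endpoints: "Resting-state functional MRI will be used to evaluate alterations in structural and functional connectivity". Neuroimaging repeats the assignment: "fMRI will evaluate structural and functional connectivity". FreeSurfer and the CONN Toolbox are named for processing. Statistical analyses covers functional connectivity and entropy and does not mention structural connectivity.

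**EEG.** For the power spectrum, "EEG data will be separated into one-second epochs after they are cleared of noise". An FFT is applied to each epoch and averaged, and the largest peak is sought in each band: delta 0.5–3.5, theta 4–7, alpha 8–13, beta 15–28 and gamma 28–48 Hz. These values go into the statistical analysis. Coherence, from task recordings, also uses one-second epochs. Only the eLORETA connectivity analysis, on eyes-closed resting data, uses recordings "separated into 2-s epochs".

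**The concern.** The Hypothesis section proposes that cognitive gains are mediated by network integrity in the PMN and DMN, as seen on fMRI and EEG. The measures above are among those meant to show this. In each case the stated input or setting does not match what the measure needs:

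- Permutation entropy needs an order, and the stated input has none that carries meaning.
- Structural connectivity needs a scan that images structure, and the stated modality is functional.
- A band edge at 0.5 Hz needs a frequency grid finer than 1 Hz.

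The first matters most, because permutation entropy is a named outcome in the statistical models. If the text is followed literally, a difference between real and sham could depend on how the region list happens to be sorted. If it is not followed, the choice of input is left until the data are in hand.

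**Working it through.** **(a) Permutation entropy**

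For order m, the normalised value is H = −Σ p(π) ln p(π) / ln(m!), where p(π) is the share of runs of m consecutive values that show ordinal pattern π. It depends on which value follows which.

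A Pearson correlation sums over time points, so it does not change when they are reordered. This was confirmed on 20 simulated autocorrelated series of 300 points: after shuffling time, the correlation matrix was identical, but the mean permutation entropy of the series themselves rose from 0.961 to 0.997. The matrix has discarded the information that permutation entropy uses.

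The only order left is the listing of regions. One 20-region matrix was simulated from 200 time points. Its 20 × 19 / 2 = 190 upper-triangle entries were read as a sequence under 1,000 random region orders for each m.

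| Measure, same matrix throughout | Minimum | Maximum | SD |
|---|---|---|---|
| Permutation entropy, m = 3 | 0.952 | 1.000 | 0.007 |
| Permutation entropy, m = 4 | 0.915 | 0.995 | 0.010 |
| Shannon entropy, 16 bins (bits) | 3.538 | 3.538 | 0 |

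A separate simulation (m = 3) set the SD from relisting one network beside the SD between different random networks in fixed order:

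| Regions | SD from relisting | SD between networks |
|---|---|---|
| 10 | 0.025 | 0.021 |
| 20 | 0.006 | 0.006 |

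The arbitrary component is about as large as the real differences among the simulated networks.

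**(b) Structural connectivity**

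No arithmetic applies. Two sections assign it to fMRI, one of them specifically to resting-state fMRI. Correlations of resting BOLD signals measure functional coupling. FreeSurfer works on anatomical images and yields regional morphometry, which is a different quantity. The analysis section gives structural connectivity no model. The endpoint is thus announced twice, tied to a modality that does not measure it, and not analysed.

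**(c) EEG resolution**

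FFT bins lie at k/T for epoch length T, so the spacing is 1/T. A bin at 0.5 Hz with T = 1 s would need k = 0.5, which does not exist.

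| Epoch | Spacing | Delta bins (Hz) | Alpha bins |
|---|---|---|---|
| 1 s | 1 Hz | 1, 2, 3 | 6 |
| 2 s | 0.5 Hz | 0.5, 1, 1.5, 2, 2.5, 3, 3.5 | 11 |

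Simulated sinusoids (500 Hz sampling assumed, 10% taper, 200 epochs averaged) gave these delta peaks:

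| True frequency (Hz) | 1 s epochs | 2 s epochs |
|---|---|---|
| 0.5 | 1 | 0.5 |
| 0.75 | 1 | 0.5 |
| 1, 2, 3 | 1, 2, 3 | 1, 2, 3 |
| 3.5 | 3 | 3.5 |

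Zero-padding, which the article does not mention, placed the 0.5 Hz signal correctly only while the epoch mean was left in; after mean removal it appeared at 0.75 Hz. At one second the other bands hold enough bins: theta 4, beta 14 and gamma 21. The 28 Hz bin falls in both beta and gamma.

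**The case against.** **On entropy**, the article points to published code and an earlier study that cannot be seen here, and the sentence on matrices may be shorthand, for example for time-resolved correlations. The simulation also had to choose an order and a way of reading the matrix, since the article gives neither. Moreover, with one fixed region list for everyone, the value is computed identically in all arms and visits, so the randomised comparison is not biased. That last point stands: the fault is one of meaning, not bias. A fixed list makes the number repeatable without making it interpretable, and a cited code does not change the input that the text states. The spread from relisting does shrink with more regions, but between 10 and 20 regions the spread between networks shrinks with it.

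**On structural connectivity**, a reader might infer that the data will contain nothing structural. The documents do not support that. This is a condensed article, scan sequences are commonly left to the full protocol, and FreeSurfer suggests an anatomical scan. Only the stated attribution to fMRI, and the absence of structural connectivity from an analysis section that names the other fMRI measures, can be faulted.

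**On EEG**, a reader might infer that the delta measure cannot be obtained at all. It can: the plan asks for the largest peak within the band, not for a 0.5 Hz peak, and one-second epochs give that peak coarsely. The plan nowhere claims to detect shifts below 1 Hz. If peak power rather than peak frequency is analysed, which the text leaves unclear, the whole-hertz steps matter less. The longer epochs used elsewhere are for resting data, so their use on task recordings is not established.

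**Conclusion.** The point holds as a mismatch between three secondary measures and their stated source or setting, in descending weight.

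- **Permutation entropy** is the main fault. As written, its value depends on an arbitrary list: 0.952–1.000 at order 3 and 0.915–0.995 at order 4 for one simulated 20-region matrix. These sizes assume simulated networks and an upper-triangle reading. The lack of time order in the matrix depends on neither.
- **Structural connectivity** is attributed to a modality that does not measure it and has no stated analysis.
- **EEG delta** is minor: three bins instead of a resolved 0.5–3.5 Hz band, assuming no zero-padding, plus one bin shared by two bands.

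It would go too far to conclude that the trial's network question fails. ROI-to-ROI and whole-brain functional connectivity, Shannon entropy and the eLORETA measures remain usable, and the primary cognitive composite and the sample size are untouched. The correction is still worth making before analysis, because it concerns named outcomes or endpoints and removes a later choice between pipelines.

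**What to change.** **(a)** State the ordered series on which permutation entropy is computed. One option is each region's BOLD time series, averaged within PMN, DMN and hippocampus; another is a time-resolved connectivity series. Keep Shannon entropy for the correlation matrix. The scans are the same, but the first option changes the construct: regional time-series entropy measures signal complexity, not network entropy, and should be named so. If the cited code already uses such a series, correcting the sentence is enough.

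**(b)** In Evaluation of the hypothesis and Neuroimaging, name the acquisition that provides structural connectivity and add its analysis. If there is none, relabel the measure as regional morphometry or remove it as an endpoint. This costs wording only.

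**(c)** Use 2-second epochs for power and coherence where the recordings allow, or restate delta as 1–3 Hz. Assign 28 Hz to one band only. Longer epochs lose slightly more data to artefact, and the task recordings must be checked first for whether they can be cut this way.

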### EEG (electroencephalogram)

*EEG Power Spectrum Analysis;* EEG data will be separated into one-second epochs after they are cleared of noise. Power spectrums of these data will be obtained in the delta, theta, alpha, beta and gamma frequency bands. Each epoch will be analyzed using the Fast Fourier Transform (FFT) with a 10% Hanning window. Subsequently, power spectrum analysis will be performed to obtain the frequency values for each electrode by averaging all FFTs. Maximum peaks will be determined in the delta (0.5–3.5 Hz), theta (4–7 Hz), alpha (8–13 Hz), beta (15–28 Hz), and gamma (28–48 Hz) frequency bands. These values will be used in statistical analysis for each person and electrode.

*EEG Coherence Analysis:* Coherence measurements at delta, theta, alpha, beta, and gamma frequencies can be analyzed for either intra-hemispheric electrode connections or inter-hemispheric electrode connections. Coherence values take values between 0 and 1. Values close to 0 indicate that there is no connection at the determined frequency between the two calculated electrode regions. In comparison, values close to 1 indicate a high coupling between the two electrode regions. Coherence calculation will be performed using the Brain Vision Analyzer program.^1^ The data obtained during memory and visualization tasks will be separated into one-second epochs after being cleared of noise. Power spectrums of these data will be obtained in the delta, theta, alpha, beta and gamma frequency bands. Fast Fourier Transform will analyze each epoch with a 10% Hanning window. Then, these data will be calculated for all possible electrode pairs using the Brain Vision analysis program with the formula given below.

*EEG functional connectivity analysis:* eLORETA software will be used for functional connectivity analysis. sLORETA/eLORETA is an online, ree software developed by Roberto Pascual-Marqui and his team^2^ (Pascual-Marqui et al., 1994). eLORETA is an algorithm developed to solve the inverse problem and it does not contain localization bias even in the presence of noise. In this software, resting state data with eyes closed, separated into 2-s epochs, whose artifacts are cleaned by pre-processing, will be used. The relevant areas to be analyzed in the cortical plane and the relevant frequency band gaps will be determined. The time series containing the eLORETA current source density obtained from these areas will be calculated, and a “lagged linear coherence” matrix will be created to be applied in graph theory (Vecchio et al., 2016). “Lagged linear coherence” will give correct physiological connectivity, unaffected by volume conduction and low spatial resolution.

### Statistical analyses

All statistical analyses will be conducted using IBM SPSS Statistics, version 29.0 (IBM Corp., Armonk, NY, United States).

Analyses will be performed stratified by diagnosis (AD-MCI and PD-MCI):

*Neurocognitive outcomes:* Within each diagnosis group, repeated-measures ANOVA/GLM will be used with Time (Baseline, Day 14, Day 90) as a within-subject factor, Group (Real vs. Sham) and Target (DLPFC vs. LPC) as between-subject factors, and age, sex, education, and baseline global cognition as covariates. Planned contrasts will test the Group × Target × Time interaction separately in AD-MCI and PD-MCI. Between-diagnosis comparisons will then examine whether the effect of stimulation differs between AD-MCI and PD-MCI by including Diagnosis (AD-MCI vs. PD-MCI) as an additional between-subject factor. Post-hoc tests will be adjusted with Bonferroni correction.

*fMRI outcomes:* Resting-state fMRI data will be analyzed separately within AD-MCI and PD-MCI groups to assess functional connectivity within DMN, PMN, and hippocampal regions, as well as entropy metrics (Shannon and permutation entropy). Longitudinal changes (Baseline, Day 14, Day 90) and group differences (Real vs. Sham; DLPFC vs. LPC) will be assessed using repeated-measures ANOVA/ANCOVA with the same covariates.

After stratified analyses, diagnosis will be included as a factor to test for Diagnosis × Group × Target × Time interactions.

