### Power calculation

The sample size was informed by previous studies applying tDCS in populations with cognitive impairment. For example, Khedr et al. administered active and sham tDCS to the left DLPFC over 10 consecutive days in 34 participants (Khedr et al., 2014). Additionally, the same group has shown efficacy of tDCS with the anode (positive electrode) placed at the T3-P3 or T4-P4 in 46 AD patients (Khedr et al., 2019).

Based on these precedents, and assuming a medium effect size (Cohen’s d ≈ 0.5–0.6) as reported in prior MCI/AD and motor adaptation studies, we calculated that a minimum of 50 participants per group would be required to achieve 90% power (1–*β* = 0.9) at a two-tailed *α* = 0.05. To allow for an anticipated dropout rate of approximately 20%, we increased the target to 60 participants in each diagnostic group (AD-MCI and PD-MCI), yielding a total sample of 120 participants. This sample size ensures sufficient power to detect clinically meaningful differences in cognitive outcomes between stimulation conditions.

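### The repeated-measures ANOVA/GLM with baseline as a Time level discards observed Day 14 scores of later dropouts and does not adjust for the outcome's own baseline: a loss mainly of efficiency

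*Protocol article*

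**What the plan says.** The Statistical analyses section fixes the software ("All statistical analyses will be conducted using IBM SPSS Statistics, version 29.0") and the model for the neurocognitive outcomes. Within each diagnosis, "repeated-measures ANOVA/GLM will be used with Time (Baseline, Day 14, Day 90) as a within-subject factor", with Group (real or sham) and Target (DLPFC or LPC) as between-subject factors. The covariates are "age, sex, education, and baseline global cognition as covariates". The planned contrast is Group × Target × Time within each diagnosis, and Diagnosis is then added as a further factor.

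The primary outcome is a composite z-score of memory measures, assessed at baseline, Day 14 and Day 90 (Evaluation of the hypothesis). Its own baseline enters as a level of the response and not as a covariate.

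The Power calculation section gives "a minimum of 50 participants per group would be required to achieve 90% power" and continues: "To allow for an anticipated dropout rate of approximately 20" percent, "we increased the target to 60 participants in each diagnostic group". The Figure 1 caption gives 20 real and 10 sham patients per diagnosis and target, hence 40 real and 20 sham per diagnosis.

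**The concern.** Two features of the stated model waste information.

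1. **Incomplete patients.** The SPSS repeated-measures GLM works on one row per patient and removes a row with any missing visit. A patient tested at Day 14 and lost before Day 90 contributes nothing, not even to the Day 14 comparison, although Day 14 is a named primary time point.
2. **Baseline as a response level.** The Group × Time contrasts then compare changes from baseline. A change score is less precise than adjustment for the same baseline value unless the visit correlation is close to 1. Global cognition is only a proxy for the baseline of the memory composite, so it recovers part of the difference.

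The Discussion itself calls the study small-scale given its multiple groups, so avoidable loss of precision matters.

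**Working it through.** **Inputs from the documents.** 60 patients per diagnosis, allocated 40 real and 20 sham; about 20% dropout; d = 0.5 (lower end of the stated 0.5-0.6); two-sided α = 0.05.

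**Assumptions not in the documents.** Equal variances; the same correlation ρ between any two visits, 0.5 to 0.9; d in units of the SD of the score; global cognition correlated r = 0.5 with the baseline composite and related to follow-up only through it.

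**Step 1: patients kept.** The plan's 60 is 50 × 1.2. At 20% dropout 60 × 0.8 = 48 remain (32 real, 16 sham), below the plan's own minimum of 50; 50/(1 − 0.2) = 62.5 would round up to 63. Whether 50 is itself adequate for real v sham is a separate matter and does not affect this point.

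**Step 2: variance per patient of the real-sham contrast at one follow-up visit** (SD of the score = 1).
- Unadjusted change score: 2(1 − ρ)
- Planned model (change, adjusted for global cognition): 2(1 − ρ) − r²(1 − ρ)²
- Own-baseline adjustment: 1 − ρ²

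| ρ | Change | Planned, r = 0.5 | Own baseline | Own/change | Own/planned |
|---|---|---|---|---|---|
| 0.5 | 1.000 | 0.938 | 0.750 | 0.75 | 0.80 |
| 0.7 | 0.600 | 0.578 | 0.510 | 0.85 | 0.88 |
| 0.8 | 0.400 | 0.390 | 0.360 | 0.90 | 0.92 |
| 0.9 | 0.200 | 0.198 | 0.190 | 0.95 | 0.96 |

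The reduction is thus 25% to 5% against an unadjusted change score, and about 20% to 4% against the planned model. Since 1/0.80 = 1.25 and 1/0.96 = 1.04, the planned model needs about 25% to 4% more patients for the same precision.

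**Step 3: power at Day 14**, real v sham within one diagnosis, d = 0.5. SE = √[v(1/n₁ + 1/n₂)], where v is the variance from Step 2; noncentral t with noncentrality d/SE and n₁ + n₂ − 6 degrees of freedom. Example, ρ = 0.5, planned model: SE = √[0.9375 × (1/32 + 1/16)] = 0.296, noncentrality 1.69, power 38%.

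| ρ | Planned, 32 v 16 | Own baseline, 32 v 16 | Own baseline, 36 v 18 | Own baseline, 40 v 20 |
|---|---|---|---|---|
| 0.5 | 38% | 45% | 50% | 54% |
| 0.7 | 56% | 61% | 66% | 71% |
| 0.8 | 72% | 76% | 81% | 85% |
| 0.9 | 95% | 96% | 97% | 98% |

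The 40 v 20 column needs every dropout to leave after Day 14; the 36 v 18 column has half leaving before. The documents do not time the dropout.

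**Step 4: Day 90.** Given baseline, Day 14 and Day 90 correlate at ρ/(1 + ρ). With 80% observed at Day 90 and the rest at Day 14 only, the variance relative to completers alone is 1 − 0.2[ρ/(1 + ρ)]²: 0.978, 0.966 and 0.960 at ρ = 0.5, 0.7 and 0.8. Partial data recover only about 2-4%; the gain at Day 90 comes mainly from own-baseline adjustment.

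**Step 5: bias**, by simulation with a true effect of 0.50 and ρ = 0.5 or 0.7. Where dropout depends on the Day 14 change, completers give 0.43-0.46 at Day 14 and 0.46-0.48 at Day 90. Where it depends on the Day 14 score by the same rule in both arms, completers give 0.47-0.48 at Day 14 and 0.50 at Day 90.

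**The case against.** - **The article does not declare a completers-only analysis.** It names no analysis population and no missing-data rule, and the analysis plan is not shown; imputation before the GLM could be specified there. This stands, so the point is limited to the model as stated and without imputation. The choice of model, with baseline as a Time level, is stated and is open to comment.
- **The loss is budgeted.** The sample size allows for 20% dropout. This also stands, although the allowance leaves 48 rather than 50. A reader might blame the model for cells falling from 20/10 to 16/8; dropout does that by itself, and at Day 90 any model observes the same reduced cells.
- **A larger power gain is tempting.** Setting an unadjusted change score on completers (36% at ρ = 0.5, 54% at ρ = 0.7) against own-baseline analysis of all 60 (54% and 71%) ignores the planned global-cognition covariate and assumes that nobody leaves before Day 14. The documents support neither step.
- **Bias.** A reader might infer that the planned estimate is biased. The shifts in Step 5 are at most 0.07 SD, against standard errors of 0.23-0.30 SD for the planned model at the same correlations, and they rest on assumed dropout rules.
- **The covariate is not shown to be weak by design.** Eligibility limits MMSE to 19-23, but the article does not say that baseline global cognition is MMSE; MoCA and CDR-SB are also collected.

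**Conclusion.** The point holds as an efficiency recommendation that should be taken up. The planned comparison is valid under randomisation, and the completers-only bias that a mixed model would remove arises only if dropout depends on early response. What is lost is precision from the outcome's own baseline, and the Day 14 scores of patients who leave later.

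The direction is firm: own-baseline adjustment is never less precise under the stated assumptions. The size depends on the unstated visit correlation, on r = 0.5 for global cognition and on when patients leave. It is worthwhile at correlations of 0.5 to 0.7 and becomes negligible for the adjustment alone at 0.9. The material does not support reading this as an invalid analysis.

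**What to change.** Within each diagnosis, fit a linear mixed model (SPSS MIXED, REML, unstructured covariance) to the Day 14 and Day 90 scores, with:
- Group, Target, Visit and all their interactions, so that the planned Group × Target contrast is kept at each visit;
- the baseline of the same outcome, and baseline × Visit;
- the planned covariates: age, sex, education and baseline global cognition.

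Include every randomised patient with at least one post-baseline score, and read effects from visit-specific contrasts. For the between-diagnosis test, add Diagnosis with its interactions up to Diagnosis × Group × Target × Visit.

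Use the same structure for EEG. For fMRI, first reconcile the scan times: the Figure 2 caption gives baseline and follow-up only, the Neuroimaging section describes a repeat right after the stimulation series but also refers to the 90th day, and the Statistical analyses section lists three times. If there is only one post-baseline scan, use ANCOVA on that scan with its own baseline.

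The cost is a revised model statement, to be fixed before unblinding, and a slightly more complex model. No new data or software is needed.
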